# Using wireless technology in clinical practice: does feedback of daily walking activity improve walking outcomes of individuals receiving rehabilitation post-stroke? Study protocol for a randomized controlled trial

**DOI:** 10.1186/1471-2377-13-93

**Published:** 2013-07-18

**Keywords:** Stroke, Rehabilitation, Walking, Physical activity, Goal setting, Technology

## Abstract

**Background:**

Regaining independent ambulation is the top priority for individuals recovering from stroke. Thus, physical rehabilitation post-stroke should focus on improving walking function and endurance. However, the amount of walking completed by individuals with stroke attending rehabilitation is far below that required for independent community ambulation. There has been increased interest in accelerometer-based monitoring of walking post-stroke. Walking monitoring could be integrated within the goal-setting process for those with ambulation goals in rehabilitation. The feedback from these devices can be downloaded to a computer to produce reports. The purpose of this study is to determine the effect of accelerometer-based feedback of daily walking activity during rehabilitation on the frequency and duration of walking post-stroke.

**Methods:**

Participants will be randomly assigned to one of two groups: feedback or no feedback. Participants will wear accelerometers daily during in- and out-patient rehabilitation and, for participants in the feedback group, the participants’ treating physiotherapist will receive regular reports of walking activity. The primary outcome measures are the amount of daily walking completed, as measured using the accelerometers, and spatio-temporal characteristics of walking (e.g. walking speed). We will also examine goal attainment, satisfaction with progress towards goals, stroke self-efficacy, and community-integration.

**Discussion:**

Increased walking activity during rehabilitation is expected to improve walking function and community re-integration following discharge. In addition, a focus on altering walking behaviour within the rehabilitation setting may lead to altered behaviour and increased activity patterns after discharge.

**Trial registration:**

ClinicalTrials.gov NCT01521234

## Background

Stroke results in sensorimotor impairments, reduced balance control, and reduced aerobic function, which can limit the capacity for independent community ambulation [1-3]. Regaining independent ambulation is important to those with stroke [4,5] and is the most frequently-reported rehabilitation goal [6,7]. Independence in walking is important for maintaining autonomy and quality of life [5,8-10]. Improved functional outcomes are observed with intense [11-13], task-specific [14-18] rehabilitation that is delivered relatively early post-stroke onset [11,16]. Therefore, if a stroke patient wishes to improve walking ability s/he should do extensive walking practice, particularly early in his/her rehabilitation. In-patient rehabilitation provides a prime opportunity for individuals with stroke to practice walking such that they can ambulate safely post-discharge. However, the amount of daily walking reportedly completed by individuals with stroke during in-patient rehabilitation is low [19-22]. Importantly, the majority of walking bouts are of short duration (<1 minute) [19,20,22,23] and typically involve walking to essential activities (e.g. washroom, dining area, or therapy) [19].

Goal setting is an essential part of rehabilitation but its use may be more ‘common sense’ rather than being grounded in sound psychological theory [24-26]. Scobbie and colleagues established recommendations for the implementation of goal-setting in rehabilitation based on three psychological theories (Figure 1): Goal Setting Theory, Health Action Process Approach, and Social Cognition Theory [25,27]. Within these recommendations, appraisal and feedback of performance were identified as important constructs [27,28]. Providing advice on health behaviours without objective feedback of compliance or outcomes may lead the patient to develop “cognitive fantasies”; i.e. belief that they are adhering to the advice when they are not [29,30]. Feedback of progress towards goals can increase motivation, improve self-efficacy and aid action-planning [28].

**Figure 1 F1:**
[figure not shown]
**Model showing the goal-setting and goal-planning process (modified from Scobbie et al., 2010; [**[27]**].** The patient may identify a broad walking goal upon admission to rehabilitation, such as “I want to be able to walk better”. The physiotherapist would discuss this goal with the patient and determine a more measurable and meaningful goal, such as “I want to be able to walk my grandson to school, which is 300m away from my house”. A short-term sub-goal is then established to help the patient progressively achieve their longer-term goal; i.e. “I want to walk 100m without stopping”. Following identification of short-term goals, a rehabilitation plan is developed and put into action. Progress towards the goal is appraised and feedback is provided to the patient; it is at this point in the goal-setting process that accelerometers can be beneficial. The appraisal will allow therapists and patients to determine if the sub-goal has been achieved. If so, a more challenging sub-goal may be developed. If the sub-goal was not achieved, the physiotherapist may modify his/her treatment plan. This cycle continues until all goals are achieved.

Researchers have begun to investigate the utility of ambulatory monitoring using accelerometers [31]. We developed the Accelerometry for Bilateral Lower Extremities (ABLE) system to specifically monitor daily walking activity in individuals with stroke [19,22]. The ABLE system combines inexpensive ‘off the shelf’ accelerometers with custom written software and provides information of each individual bout of walking completed throughout the patients’ day. Therefore, the system can provide feedback to the patient or therapist on not only the total amount of walking completed in the entire day, but also the duration of each walking bout (i.e. how long the patient walked continuously) and times of day when the patient was active or inactive. Furthermore, by placing accelerometers on both lower limbs, we can provide information regarding the control of walking throughout the day (i.e. temporal features of gait). This information can be provided to the patient and his/her physiotherapist as part of a goal-setting process in order to determine whether the patient’s goals for ambulation are met.

The primary objective of this study is to determine if feedback about characteristics of daily walking activity, provided to patients and their treating therapists, will increase walking activity in a group of individuals receiving rehabilitation post-stroke. We hypothesize that, compared to a control group who do not receive feedback via the treating physiotherapists, those who receive accelerometer-based feedback of daily walking activity as part of a goal-setting process will show: increased total daily walking activity, as measured by number of steps per day, total duration of walking activity, and total distance walked; increased frequency of ‘long’ walking bouts (i.e. > 5 minutes in duration); and improved control of walking, as defined by increased self-selected walking speed, and improved symmetry in spatio-temporal characteristics of walking. While walking practice should be initiated during in-patient rehabilitation, problems with walking function may not be fully apparent until the patient is discharged home. Therefore, we will examine the effects of accelerometer-based feedback administered during both in- and out-patient rehabilitation. Under the assumption that accelerometer-based feedback will increase walking activity, the secondary objective of this study is to determine if increased walking activity during rehabilitation results in increased rates of goal attainment, increased satisfaction with rehabilitation, improved self-efficacy, and improved community re-integration post-discharge from rehabilitation.

## Methods

### Design overview

This is a single-blind randomized controlled trial with the assessor being blinded to the group allocation (participants cannot be blinded to group allocation). Participants will be randomly assigned, using allocation concealment, to one of two groups: feedback or no feedback. The study will span three phases of rehabilitation and recovery post-stroke: in-patient rehabilitation, out-patient rehabilitation, and post-rehabilitation community reintegration. Outcome measures will be obtained at up to four time points (Figure 2): 1) upon entry into the study; 2) immediately prior to discharge from in-patient rehabilitation; 3) immediately prior to discharge from out-patient rehabilitation (for those admitted to out-patient rehabilitation at the institution); and 4) three months following discharge from rehabilitation. This study was approved by the University Health Network research ethics board (protocol number 11-027-DE).

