### Intervention

Participants will be recruited into the study when they are deemed to be ambulatory without supervision. Patients with stroke tend to be discharged from in-patient rehabilitation 2–4 weeks after they reach this status. Therefore, the length of the in-patient intervention phase will vary between participants but will be approximately 2–4 weeks long. Out-patient rehabilitation services are offered in three blocks of 4–6 weeks duration; the first block is 6-weeks long to allow extra time for assessment prior to prescription of rehabilitation services. Participants in this study will be followed only for the first and second (if applicable) block of out-patient rehabilitation. The third block is often either not completed at all or not completed immediately subsequent to the second block (i.e. there may be a gap of a number of months between the second and third block). Therefore, the duration of the out-patient phase of the intervention is 6–10 weeks.

In order to ensure that all physiotherapists administer the intervention in a consistent manner, we will host a series of in-services concerning goal-planning of walking activity. These in-services will focus specifically on the output from the ABLE system, which is the new component of this study. Physiotherapists will learn how to interpret the output from the ABLE system and how to use this information to evaluate a patient’s progress towards their goals. Specific cases will be discussed based on pilot testing of ambulatory monitoring.

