#### In-patient rehabilitation phase

Participants in both intervention groups will meet with their primary treating physiotherapist once per week to discuss progress towards their goals for rehabilitation that are relevant to physiotherapy, including goals for walking. All participants will wear the accelerometers every weekday during in-patient rehabilitation to monitor daily walking activity. Research personnel will meet with the patients each morning to ensure that the accelerometers are worn correctly.

For those participants assigned to the feedback group, physiotherapists will receive a daily summary of patients’ walking activity as a tool to guide goal planning. Physiotherapists will use the information as a ‘homework checker’ to determine if patients are complying with an assigned walking program. In the case of non-compliance, the physiotherapist will discuss a coping strategy for better integrating walking activity into the patients’ day. In the event that the patient is meeting their specific sub-goals for walking activity, the physiotherapist will re-evaluate these sub-goals and suggest more challenging goals.

For participants assigned to the control group, physiotherapists will not receive accelerometer-based feedback of daily walking activity. However, physiotherapists will still discuss the achievement of walking goals with their patient. The same strategies implemented in the feedback group will be implemented in the control group (i.e. action plans, coping strategies, re-evaluation of goals). This process is no different to usual care around goal planning at Toronto Rehab.

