#### Primary outcomes – daily walking activity & control of walking

The primary outcome measures pertain to walking activity as averaged over three days around the first two assessment time points (i.e. enrolment into the study and discharge from in-patient rehabilitation), and over seven days before the last assessment time point (discharge from out-patient rehabilitation). A longer monitoring period will be used for the out-patient phase as patients have more options for mobility post-discharge. Summary, whole day, outcome measures will be used in the analysis; i.e. total walking duration, total number of steps taken and total distance walked. However, it is most relevant to community ambulation and aerobic fitness to show increased duration of continuous walking [46,47]; therefore, we will also calculate the frequency and duration of longer walking bouts (i.e. >5 minutes continuously). Furthermore, intensity of walking is also important for cardiovascular benefit; therefore we will determine the frequency and duration of ‘high intensity’ walking, defined by either a walking speed or cadence ≥ 85% of maximum walking velocity.

Increased walking practice should improve control of walking. Spatio-temporal features of self-selected walking will be measured using a 4 m-long pressure sensitive mat (GAITRite, CIR Systems, Inc, Havertown, Pennsylvania, USA). Participants will start walking at least 1 m away from the mat and will be instructed to walk across the mat until they reach a mark 1 m from the end of the mat. Participants will be instructed to walk at their normal pace. Participants will complete three passes across the mat and measures will be averaged across the three passes. Walking speed, cadence, step length, and symmetry of spatio-temporal measures [48] will be calculated. While it is possible to determine these measures from the daily walking activity collected using the ABLE system, standardized assessment is required for pre- to post-intervention comparison of spatio-temporal measures.

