For sample size estimates, we used change in total walking duration from the initial assessment to discharge from in-patient rehabilitation (i.e. the first phase of the study) as our primary outcome of interest. In our pilot work, we observed an average increase in total daily walking activity of 20 minutes from the initial assessment to discharge in a group of stroke in-patients. We expect that an average increase in daily walking activity of 40 minutes in the feedback group would be clinically meaningful (i.e. 20 minutes more than expected with no feedback). The standard deviation for change in daily walking time was 23 minutes in our pilot work. Using a sample size formula for repeated measures ANOVA [58], an improvement of 20 minutes of walking more in the feedback group than the no feedback group, a standard deviation of 23 minutes, a probability of a Type I error of 0.05 and probability of Type II error of 0.1, 28 individuals per group will be required in the final analysis. In order to achieve a final sample of 56 (i.e. 28 per group) we will aim to recruit approximately 62 participants (i.e. assuming that approximately 10% of participants will withdraw from the study). Sample size and power estimates using an updated standard deviation will be reassessed after the first 12 participants have completed the first phase of the study, as per CONSORT recommendations [59,60].

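### The main walking comparison is read at in-patient discharge, so gain mixes with time in hospital if stay differs by arm, and the planned length-of-stay covariate is an unsound safeguard

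*Protocol article*

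**What the plan says.** Under Statistical analyses and sample size, the trial is sized on "change in total walking duration from the initial assessment to discharge from in-patient rehabilitation". Design overview places that second assessment "immediately prior to discharge from in-patient rehabilitation", so it is tied to an event and not to a fixed time from randomisation. The Intervention section says that "the length of the in-patient intervention phase will vary between participants but will be approximately 2–4 weeks long". Walking activity is "averaged over three days around the first two assessment time points", and the analysis section defines its time factor as the assessment point, not elapsed days.

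More data than this are recorded. The In-patient rehabilitation phase section states: "All participants will wear the accelerometers every weekday during in-patient rehabilitation to monitor daily walking activity".

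On recovery under usual care, the authors report that in pilot work "we observed an average increase in total daily walking activity of 20 minutes from the initial assessment to discharge". On blinding, Design overview says: "This is a single-blind randomized controlled trial with the assessor being blinded to the group allocation". Group allocation and blinding has the treating physiotherapists deliver the feedback, so they know the arm.

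The one provision that touches timing is in Statistical analyses and sample size. In-patient length of stay is listed with four clinical scales as a potential confounder, is compared between groups, and enters the model as a covariate if the groups differ significantly.

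**The concern.** Walking increases with time in usual care, so the gain from enrolment to discharge is partly a matter of how long the patient stayed. The stated range for that interval is two-fold.

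The intervention aims to speed progress towards walking goals, and the physiotherapists who apply it are unblinded. It is plausible, though not documented, that mean stay could differ by arm in either direction. Quicker progress could bring discharge forward; harder sub-goals could lengthen the stay. The discharge difference would then combine two things: how fast walking improved, and for how long it was allowed to improve. A two-point analysis cannot separate them.

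The planned safeguard does not solve this. Length of stay is determined after randomisation and may itself be affected by treatment, so adjusting for it can remove part of the effect or introduce bias. Whether adjustment happens at all depends on a significance test in a small sample.

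**Working it through.** **The plan's own figure.** Inputs from Statistical analyses and sample size: difference 20 minutes, SD of change 23 minutes, Type I error 0.05 (taken as two-sided), power 0.90.

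n per group = 2 × [23 × (1.960 + 1.282) / 20]² = 27.8, rounded up to 28. This reproduces the stated number. A two-sample t-test with 28 per group has power 0.89.

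**Illustration of the timing effect.** Assumptions not in the documents: gain is linear in time, and the expected gains of 20 and 40 minutes are reached after a mean of 3 weeks. Weekly gains are then 20/3 = 6.7 minutes (control) and 40/3 = 13.3 minutes (feedback).

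If feedback patients leave w weeks earlier and controls stay 3 weeks, the difference at discharge is (40/3) × (3 − w) − 20. Power is for a two-sided t-test, 28 per group, SD 23:

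| Feedback arm leaves earlier by | Difference at discharge | Power |
|---|---|---|
| 0 weeks | 20 min | 0.89 |
| 0.5 week | 13.3 min | 0.57 |
| 1 week | 6.7 min | 0.19 |

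The weekly gain is doubled by feedback in every row.

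The pilot interval is not stated, so the half-week case was repeated with the gains reached at other mean stays:
- 2 weeks: 20 × 1.5 − 20 = 10 minutes, power 0.36.
- 4 weeks: 10 × 3.5 − 20 = 15 minutes, power 0.67.

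**The other direction.** With no effect on the rate of gain, one extra week of stay in the feedback arm gives a 6.7-minute difference on the 3-week base, or 5 to 10 minutes across bases of 4 to 2 weeks. It would be declared significant with probability 0.19 (range 0.13 to 0.36), against a nominal 0.05.

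**The length-of-stay screen.** This is the probability that a true difference in mean stay reaches two-sided 5% significance with 28 per group. The SDs of stay are assumed, as none is given:

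| SD of stay | True difference 0.5 week | True difference 1 week |
|---|---|---|
| 0.58 week (stay uniform over 2–4 weeks) | 0.89 | above 0.99 |
| 1 week | 0.45 | 0.96 |
| 1.5 weeks | 0.23 | 0.69 |

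For a half-week difference, which already costs a third of the effect in the illustration (6.7 of 20 minutes), the screen misses more often than not unless stay is tightly distributed. When it does trigger, the model conditions on a post-randomisation variable. If stay is counted from admission, it also includes time before enrolment, because patients are recruited during their stay. It is then not the interval over which the gain accrues.

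**Data already available.** Two to four weeks of weekday recording gives about 10 to 20 days per participant, of which the planned analysis uses three at each end.

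**The case against.** A reader might infer that the unblinded team will shift discharge, that the discharge comparison is therefore biased, or that the trial is underpowered. The documents support none of these.

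- **Who sets the date.** No section gives discharge criteria or says who decides. The protocol's stated response to faster progress is harder sub-goals, not earlier discharge. Goals may also be recorded as only partly achieved or not completed, so discharge does not wait for goal attainment. A difference in stay by arm is an inference.
- **The estimand.** Walking at discharge, compared as randomised, is a legitimate target. It includes any effect that runs through length of stay. The rate of gain at a fixed time is a different question, and a gap between the two is not in itself an error.
- **The sizing.** The 40-minute expectation is for gain measured at discharge, so any change in stay may already be inside it. The illustration moves it to a fixed 3 weeks, and the shifts of half to one week are assumed. Full cancellation needs extreme values, such as mean stays of 2 and 4 weeks.
- **The remedy.** A model by elapsed time relies on discharge depending on walking already observed. At 3 weeks many patients will have gone home.
- **The analysis plan.** A supplementary elapsed-time analysis could sit in a statistical analysis plan that is not shown.

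All of this stands as a limit on the point. It does not rescue the length-of-stay covariate, which the article itself fixes. Blinded assessment and accelerometry protect how walking is measured, not when.

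**Conclusion.** The point holds in a limited form. If mean stay is the same in both arms, reading the outcome at discharge introduces no bias. If stay differs, the result at discharge cannot show how much is faster improvement and how much is time in hospital. The only stated safeguard is a significance-triggered adjustment for a variable that treatment may affect.

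The loss of power from 0.89 to 0.57 or 0.19 shows possible size only; it rests on linear gain, a 3-week mean stay and assumed shifts. The low power of the screen rests on assumed SDs of 1 to 1.5 weeks and a half-week difference. The weakness of conditioning on a post-randomisation variable needs no such assumption. The figure of 28 per group is correct on its inputs.

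**What to change.** 1. Remove in-patient length of stay from the list of candidate covariates. Report it by arm as an outcome, counted from randomisation.
2. Keep the comparison at discharge.
3. Add a prespecified longitudinal model of daily walking duration from the weekday in-patient recordings, by days since randomisation, with arm-by-time terms. Report the arm difference at a fixed time that nearly all participants reach as in-patients, for example 2 weeks. Label any 3-week estimate as more model-dependent.
4. State the model's assumption that discharge depends on walking already observed. Use the estimate to interpret the discharge result, not as a second condition for success.

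The cost is analysis wording and processing of recordings already made, with no extra visits. The drawback is that an early fixed-time estimate reflects less exposure to feedback than the discharge reading does in patients who stay longer.
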